Although many studies have reported the biological basis of psychiatric disorders, none have been put into practical use or are useful in clinical practice. Particularly, resting-state functional magnetic resonance imaging (rs-fMRI) is expected to be put into practical use owing to its safety and provision of a large amount of information. However, there is a great difficulty in practical use because the nature of the data differs depending on the measurement facility. Therefore, we integrated rs-fMRI data acquired at multiple institutions by the harmonization method using traveling individuals as homogeneous large-scale data (total of 1,584 cases) [5] and subsequently applied a cutting-edge machine learning method to develop a brain network marker for MDD diagnosis [6]. This brain network marker can distinguish between healthy individuals and patients with MDD with a probability of approximately 70%, even for completely independent data obtained at different facilities [6]. Therefore, we designed this study as a clinical trial to establish anterograde evidence for the practical application of this brain network marker for MDD diagnosis (diagnostic marker) as Software as a Medical Device. In addition, we developed brain network markers for MDD stratification (stratification marker) with robustness among independent datasets by performing unsupervised machine learning on rs-fMRI data of patients with MDD [7]. Statistically significant differences were also observed in the therapeutic responsiveness to escitalopram between the MDD subtypes discriminated by these brain network markers. Therefore, the anterograde verification of these stratification markers was set as the secondary endpoint of this study. The results of this study will provide useful information for the diagnosis and treatment selection of MDD using rs-fMRI.

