### Primary and secondary endpoints

The primary endpoint will be the area under the curve (AUC) of the receiver operating characteristic (ROC) curve when distinguishing between patients with MDD and HCs using the depression probability value calculated from the diagnostic marker at week 0.

The following will be the secondary endpoints:

Longitudinal evaluation of the diagnostic marker: The depression probability value, which is the output of the diagnostic marker, will be analyzed with two factors: remission/non-remission and time of treatment (0 w, 6 w, 6 m). Remission has been defined as a depression severity of 7 points or less using the Hamilton Rating Scale for Depression (HRSD).Depression severity will be obtained longitudinally (0 w, 6 w) in the escitalopram group; we will compare the rate of symptom improvement evaluated using the HRSD among the subtypes identified by the stratification markers in the escitalopram group.Depression severity will be obtained longitudinally (0 w, 6 w) in the usual care group, and we will compare the rate of symptom improvement evaluated using the HRSD among the subtypes identified by the stratification markers in the usual care group.

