### The target number of participants and the basis for setting

The target number of participants in each group is as follows:

Escitalopram group: 80 participants.Usual care group: 60 participants.Cross-sectional study group: 200 participants.HCs: 50 participants.

The number of cases required for the main examination in this study was calculated as follows:

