The number of participants required to verify that patients with MDD and HCs can be distinguished using a “diagnostic marker” was set based on the following criteria. The AUC was approximately 0.77 in the data of our previous study. [6] Assuming that the AUC is 0.65 conservatively and calculating the sample size (http://www.biosoft.hacettepe.edu.tr/easyROC/) that can detect AUC > 0.5 with Type, I error: 0.05 and power: 0.8, 43 participants will be required for each group. Assuming a 10% chance of cancellation or dropout, it was considered appropriate to aim for 50 registrations per group.The reasons for setting the number of cases required to verify whether the rate of symptom improvement among the MDD subtypes identified by the stratification markers in the escitalopram group differed significantly are as follows. Based on a power analysis for the Mann–Whitney U test using the method developed by Shieh et al. [10], the sample size calculation was performed with Type I error 0.05, power: 0.8 using R’s shiehpow function (https://www.rdocumentation.org/packages/wmwpow/versions/0.1.3/topics/shiehpow). Therefore, 68 participants will be required. Predicting approximately 10% cancellation or dropout, it was considered appropriate to aim for the registration of 80 participants.Based on past medical records, approximately 60 and 200 patients are expected to be eligible for the usual care group and cross-sectional study group within the registration period, respectively. The data obtained from the escitalopram and usual care groups will be used to determine whether the “brain network marker of MDD diagnosis” reflects the therapeutic effects in patients with depression (Purpose 2). In addition, we will conduct exploratory investigations to determine whether there is a significant difference in the rate of symptom improvement between subtypes by “stratification markers” in the data of the usual care group combined with the data that XNef, Inc. possesses (Purpose 4). Furthermore, the MRI data obtained from all groups will be used as training data to improve the accuracy of the AI program that assists in diagnosing MDD (Purpose 5). Based on these findings, obtaining as much data as possible from eligible patients in non-interventional groups is desirable. Therefore, although it is difficult to imagine a situation where the expected number of cases is significantly exceeded in reality, if the expected number of cases is exceeded, all patients who have provided consent within the registration period should be allowed to be enrolled.

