### Analysis of secondary endpoints

The patients will be grouped into remission and non-remission groups based on the severity of depression at 6 weeks and 6 months, using the escitalopram and usual care groups as the populations to be analyzed. The depression probability value will be analyzed for two factors using these data: remission/non-remission *treatment time point (0 w, 6 w, 6 m), and a test will be conducted at a significance level of 5%.

With escitalopram as the target group for analysis, patients with MDD will be stratified using stratification markers. The rate of symptom improvement evaluated using the HRSD will be compared between depression subtypes and tested at a significance level of 5%.

Patients with MDD in the usual care group combined with the data from XNef, Inc. will also be stratified using the stratification markers. The rate of symptom improvement evaluated using HRSD will be compared between depression subtypes and tested at a significance level of 5%.

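### The third secondary endpoint is defined in the usual care group alone but tested only in data pooled with company-held patients, with subtype as the only named factor, so data source can confound the comparison.

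*Protocol article*

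**What the plan says.** Three sections of the protocol article bear on this analysis, and they do not describe the same one.

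- **Primary and secondary endpoints.** The third secondary endpoint compares HRSD improvement from week 0 to week 6 "among the subtypes identified by the stratification markers in the usual care group". No outside data are mentioned.
- **Analysis of secondary endpoints.** The only analysis that corresponds to it uses a larger population: "Patients with MDD in the usual care group combined with the data from XNef, Inc. will also be stratified using the stratification markers". Then: "The rate of symptom improvement evaluated using HRSD will be compared between depression subtypes and tested at a significance level of 5" per cent. No test, sidedness, source factor, stratum or trial-only result is given.
- **The target number of participants and the basis for setting.** The pooling is repeated, "in the data of the usual care group combined with the data that XNef, Inc. possesses", and tied to Purpose 4. Here its status is lower: "we will conduct exploratory investigations to determine whether there is a significant difference in the rate of symptom improvement between subtypes". The trial's own contribution is "Usual care group: 60 participants", an expected count from past records and not the result of a power calculation.

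The Background says of rs-fMRI that "the nature of the data differs depending on the measurement facility". Under MRI acquisition, all trial scans come from one scanner at one university. The number, scanner, treatment, severity and assessment times of the company-held patients are not described.

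**The concern.** Subtypes are assigned from rs-fMRI, so two sources scanned under different conditions, or recruited differently, may have different subtype mixes. Improvement may differ as well: usual care patients have no restriction on antidepressants, and the group takes patients who are not suitable for escitalopram or cannot continue it. Nothing is said about how the company-held patients were treated.

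If both the subtype mix and mean improvement differ by source, source confounds the subtype comparison. Part of the difference between sources then appears as a difference between subtypes, or cancels a real one. Because the analysis section gives no trial-only result, a reader following the text would have only the pooled figure for an endpoint that was defined in trial patients.

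**Working it through.** The article states no sample size, power or effect size for the pooled test, so there is no figure to reproduce.

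**Inputs from the article:** 60 usual care patients; 5% level; subtype as the only named factor.

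**Assumed inputs:** 60 company-held patients; two subtypes; two-sided test; normal outcomes with SD 1 within source; subtype shares that mirror each other between sources (for example 60% and 40%); a mean difference d between sources.

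**Bias.** With 60 + 60 patients and shares p and 1 − p, each subtype has 60 patients. The proportion of trial patients is p in one subtype and 1 − p in the other. With no true subtype effect, the expected pooled difference is

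bias = (2p − 1) × d.

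This is a product. It is zero if the shares are equal (p = 0.5) or if improvement does not differ by source (d = 0), so both must differ.

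**Approximate type I error.** Variance within a subtype is 1 + p(1 − p)d², SE = √(2 × variance/60), and k = bias/SE. Rejection probability = P(Z > 1.96 − k) + P(Z < −1.96 − k).

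- p = 0.60, d = 0.3: bias 0.06, SE 0.1845, k = 0.33; 0.051 + 0.011 = 6.2%.
- p = 0.60, d = 0.5: bias 0.10, SE 0.188, k = 0.53; 0.076 + 0.006 = 8.3%.
- p = 0.65, d = 0.5: bias 0.15, SE 0.188, k = 0.80; 0.123 + 0.003 = 12.6%.

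**Simulation**, Mann-Whitney on the pool against the source-stratified van Elteren test, 6,000 data sets per scenario, 60 + 60 patients. Where two values are shown, they come from separate sets of runs:

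| Shares | d (SD) | Pooled | Stratified |
|---|---|---|---|
| 50/50 | 0.5 | 5.3% | 5.2% |
| 60/40 | 0 | 4.9% | 4.9% |
| 60/40 | 0.3 | 5.9% | 4.5% |
| 60/40 | 0.5 | 8.3%, 8.9% | about 5% |
| 65/35 | 0.5 | 11.7%, 13.0% | about 5% |
| 70/30 | 0.5 | 17.4% | 5.2% |

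The simulation agrees with the hand calculation. With 30 to 120 company-held patients, the 60/40, 0.5 SD case ranges from 6.6% to 9.5%.

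**Masking.** With a true 0.5 SD subtype effect, d = 0.5 and the source imbalance working against the effect, pooled power is 51 to 53% at 60/40 shares, against 72% stratified. At 70/30 it is 33% against 66%. With the imbalance working in the same direction at 70/30, the pooled test rejects in 95% of data sets, against 66% stratified.

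**What stratifying costs.** Information on the subtype contrast is proportional to the sum over sources of n × p × (1 − p). With equal shares this is 2 × 60 × 0.25 = 30. At 60/40 it is 2 × 60 × 0.24 = 28.8 (4% less), and at 70/30 it is 2 × 60 × 0.21 = 25.2 (16% less). Simulated power with no source difference in improvement, pooled against stratified, is 75% against 75% at 50/50, 75% against 73% at 60/40, and 75% against 67% at 70/30.

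**The case against.** The strongest reply is that the article does not specify an unstratified test. It names no test for this comparison. The Mann-Whitney test appears only in the sample-size calculation for the escitalopram group. Strata and covariates for a secondary analysis are commonly left to an analysis plan, which is not shown. A reader might infer that the sponsor has decided to ignore data source, but the text does not support that: it is silent. This part of the objection stands, and the point here does not rest on the silence. It rests on what the article does fix: the pooled population, the subtype contrast, the 5% level, and an endpoint definition that names a different population.

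Three further replies have some force.

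- The Background also says that the stratification markers were developed to be robust across independent datasets. That makes a scanner-driven shift in subtype share less certain. It does not make subtype shares equal in two differently recruited cohorts.
- The pooled analysis is called exploratory and affects neither the primary endpoint nor the powered escitalopram comparison. That limits the consequence. It does not remove confounding, and the same analysis stands in the secondary-endpoint section with a 5% test.
- Stratifying is not free, as the 70/30 case shows.

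**Conclusion.** The concern holds in a limited form. The endpoint definition and the analysis section name different populations, and the pooled analysis as written provides no protection against confounding by data source. That needs correcting, with modest consequences, because the pooled work is labelled exploratory.

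A reader might conclude that the 5% level fails as soon as the two sources differ. It does not: with a difference in subtype share alone, or in improvement alone, the error stays near 5%. When both differ, the inflation is small at moderate imbalance (about 6% to 9% at 60/40 shares) and larger beyond that (12 to 13% at 65/35 with 0.5 SD). Apart from the 60 usual care patients and the 5% level, every input is an assumption. The article gives nothing from which the true shares or the source difference could be estimated, so these figures show what could happen and do not predict the result.

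**What to change.** 1. In Analysis of secondary endpoints, add the subtype comparison in the usual care group alone, as Primary and secondary endpoints defines it, and make that the result for the endpoint.
2. Keep the pooled comparison and label it exploratory there too, in line with the sample-size section.
3. State that the pooled comparison is stratified by data source (for example the van Elteren test) or adjusted for it (source as a factor in a model), and show the subtype difference separately for trial and company-held patients.

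The cost is a few sentences and little extra analysis, with no added patients or visits. On the assumed inputs, stratifying loses almost no power when subtype shares are similar, and about 8 points (roughly 75% to 67%) if shares are 70/30 and improvement does not differ by source. The usual care group alone gives a less precise result than the pool. With about 60 patients it should be read as an estimate with its interval, since that number was not set by a power calculation.

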### Monitoring and auditing

A person in charge of monitoring will be appointed, and monitoring will be conducted to confirm whether this research is being conducted safely and per the study protocol and whether data are being collected accurately.

When investigators become aware of the occurrence of a disease or malfunction, they will immediately take appropriate measures, such as discontinuing the intervention and entering the information into the Electronic Data Capture without discrepancies.

Data management, statistical analysis, monitoring, and auditing will be outsourced to SRD Co. Ltd.

To ensure the quality of clinical research, the auditor will confirm that it is being conducted appropriately by directly viewing the source documents.

### Patient and public involvement

No patient was involved.

## Dissemination

The findings from this study will be published in peer-reviewed journals and presented at local, national, and international conferences. In addition, the main results will be published on the jRCT website (https://jrct.niph.go.jp/). Hiroshima University and XNef, Inc. will be credited with disseminating both preliminary and final results.

## Discussion

Given fMRI can non-invasively evaluate changes in brain activity with a high spatial and temporal resolution, it has been applied to research on psychiatric disorders, and many results have been reported. For clinical applications, rs-fMRI is attracting attention as a method that can evaluate brain activity without frequently difficult tasks in patients with cognitive and motivational deficits. Initially, analyses were performed to detect statistically significant differences by comparing patients and HCs; however, recently, machine learning methods aimed at discrimination at the individual level have been used. Meta-analyses [15, 16] of such studies have shown good discriminative results, raising expectations for clinical applications. However, it has been highlighted that when commonly used machine learning methods are applied to a small data sample of dozens of individuals, overfitting causes inflation in leave-one-out cross-validation discriminant results, resulting in poor generalization performance to independent external data [17]. Our diagnostic marker [6], which was developed by integrating fMRI data acquired at different facilities as large-scale data by harmonization using traveling individuals [5], has a generalization performance to multiple external independent data with an accuracy of approximately 70%. Therefore, it is considered suitable for prospective clinical research aimed at practical applications. In this study, we will confirm that sufficient accuracy of the diagnostic marker [6] could be reproduced for data from a prospective clinical study.

The diagnostic marker developed by supervised machine learning, which treats DSM diagnosis as the correct answer, cannot address the heterogeneity of MDD. As recently proposed [18], it is necessary to classify patients into homogeneous subtypes from the viewpoint of brain function using unsupervised machine learning methods, including clustering without diagnostic labels, and subsequently evaluate the validity of the classification based on outcomes, such as response to specific treatments. Based on this idea, we previously used the Bayesian multiple co-clustering methods to analyze multidimensional data of patients with MDD and reported that functional connectivity of the brain centered in the right angular gyrus and childhood traumatic experiences categorized the patients into three groups, one of which was less responsive to selective serotonin reuptake inhibitor treatment [19]. However, in addition to the fact that the study was conducted on a relatively small sample size and the reproducibility was not verified, there were limitations, such as using psychological experiences for classification. A study by Drysdale et al., using large multicenter rs-fMRI data, classified patients with MDD into four subtypes according to the functional connectivity patterns of the limbic and frontostriatal networks. Furthermore, the subtypes differed in their responsiveness to transcranial magnetic stimulation therapy. However, a study reproducing the analysis pipeline of Drysdale et al. and analyzing different clinical data sets failed to validate subtype stability [20]. Therefore, the development of reproducible stratification biomarkers is of paramount importance. Recently, we successfully created generalizable stratification markers [7]. However, in the current diagnosis and treatment of MDD, no objective biomarker exists, and treatment is performed by trial and error based on the experience of doctors. Our brain network markers for MDD diagnosis and stratification can overcome this situation. We can provide advanced diagnostics and treatments by verifying and putting them into practical use.

This study design has some limitations, including that our imaging protocol developed in the Strategic Research Program for Brain Sciences (November 2013 to March 2018) has a lower signal-to-noise ratio and resolution than the latest imaging protocols, such as the Harmonization Protocol (HARP) [21]. However, multicenter data collection has just begun regarding the HARP protocol, and there is still no evidence for creating generalizable biomarkers for psychiatric disorders. Therefore, it is necessary to aim for the clinical application of a protocol that already has evidence. Although with some limitations, the data collected in this study will be crucial for the clinical application of brain network markers for MDD diagnosis and stratification.

## Data Availability

Not applicable.

## Abbreviations

MDD: Major depressive disorder
DSM: Statistical Manual of Mental Disorders
rs-fMRI: Resting-state functional magnetic resonance imaging
HCs: Healthy controls
AUC: Area under the curve
ROC: Receiver operating characteristic
HRSD: Hamilton Rating Scale for Depression
MINI: Mini International Neuropsychiatric Interview
ROI: Region of interest
BOLD: Blood oxygen level-dependent
HARP: Harmonization Protocol
